### Feasibility methodology

#### Participants, setting, and sample size

Participants will be patients referred for consultation for *de novo* ICDs for prophylaxis against sudden cardiac death. Exclusions are: 1) unable to understand the decision aid due to a language barrier or visual impairment, and 2) referral for an ICD with cardiac resynchronization or secondary prevention indication. To assess the feasibility of a conducting a larger trial, we will enroll 80 patients (40 per arm) over 10 months. The sample size for this pilot trial was based primarily on feasibility considerations. This pilot RCT will inform the estimates of effect sizes and variance for a larger trial.

### Baseline visit

Members of the healthcare team will introduce the study to patients after ICD candidacy is determined but prior to their consultation in which the decision may be discussed/made. Introduction of the study will take place by mail or phone after candidates are contacted by the health care team to confirm the consultation appointment. Following the introduction to the study, the research assistant (RA) will either mail patients a study package, or arrange to meet patients for a baseline visit prior to the specialist consultation visit. At the time of the baseline visit, the RA will review study procedures, and obtain written consent. Following consent, the RA will collect baseline demographics, medical history, heart failure classification (NYHA), HRQL, and depressive symptoms. Once complete, the RA will randomize the patient.

### Allocation

We will randomly allocate patients to intervention (PtDA *prior* to specialist consult) or usual care. We will use a secure electronic randomization system (http://www.randomize.net/). The allocation sequence is concealed. The research assistant will enroll participants and access the randomization system to determine group assignment following baseline data collection (see below).

### Blinding

Because of the nature of the intervention, patients assigned to PtDA, and the RA, will not be blind (to decision aid or usual care). Data analysts will be blind to treatment assignment for outcomes measured in both groups (knowledge, HRQL, preference, health/personal priorities, decisional conflict pre/post, and decisional outcomes). Participants and the RA will not be aware of treatment assignment during baseline data collection.

### Intervention

The intervention group will receive and use the PtDA with a trained research assistant *prior* to specialist consultation.

### Usual care

The usual care group will receive standard HHS information upon arrival for their specialist consultation.

### Visit one - pre consultation

#### Baseline measurements - (intervention and usual care)

To measure baseline psychosocial status and HRQL, we will use The Medical Outcomes Trust Short Form (SF-36v2), a generic HRQL scale used extensively in health care and ICD research. The reliability and validity of the SF-36v2 is well established [63]. The Center for Epidemiologic Studies Depression Scale will measure depressive symptoms (CES-D) [64]. The CES-D has demonstrated good reliability and validity across different community and clinical settings [65]. The NYHA [66] classifies functional abilities based on self reported symptom limitations; it has strong predictive utility and is used widely in practice. Participants will also rank their five priorities (health and personal).

Patients randomized to the intervention group will complete the PtDA and decision quality measures (values, decisional conflict, and knowledge). The usual care group will complete decision quality measures (decisional conflict, knowledge). Both groups will complete these measures prior to specialist consultation if feasible.

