### Evidence to inform the calculation of a sample size for a larger trial

The pilot RCT will inform estimates of effect sizes and variance for a larger trial. More specifically, we will identify clinically significant differences in the change scores of decision quality measures (Decisional Conflict) that correspond to acceptable levels of patient uncertainty about their course of action (treatment options).

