### Data collection, management and analysis

Results for feasibility outcomes including participant recruitment, referral rates, patient uptake of the decision aid, and missing data will determine feasibility of study processes. This will mainly be descriptive in nature. Continuous variables will be summarized using descriptive statistics and measures of central tendency (means, standard deviations) and categorical variables using percentages and frequencies. Assumptions of the normality of data will be assessed. When normality assumptions are not met, non-parametric tests will be applied [73]. To determine differences in decision quality (Decisional Conflict) each group’s scores will be compared using independent sample *t*-test at two time points. The first comparison will be within group (pre and post consultation) followed by 2) between group differences in the change scores using analysis of covariance (ANCOVA) that adjust for baseline scores [73]. All quantitative tests will be two-sided and conducted at the 5% level of significance. We will also use knowledge scores > 66% to predict decision choice using logistic regression techniques. To examine associations between baseline HRQL, depressive symptoms, and 1) decision choice, and 2) values, we will use regression analysis and calculation of odds ratios and 95% confidence intervals where appropriate. SAS 9.2 (Cary, NC, USA) will be used to conduct quantitative analyses.

Qualitative data (interviews, field notes) will be analyzed using interpretive descriptive analysis [74-76]. Interviews will be recorded, transcribed verbatim, and anonymized. NVivo (http://www.qsrinternational.com/contact.aspx) software will assist with the management and coding of findings. We will analyze patient interviews to identify themes surrounding patient perceived barriers to decision aid uptake.

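### The Decisional Conflict score used as baseline is taken after randomisation, and probably after the decision aid, so the change-score ANCOVA shrinks and can reverse the aid's effect

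*Protocol article*

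**What the plan says.** **Before randomisation** (Baseline visit): "Following consent, the RA will collect baseline demographics, medical history, heart failure classification (NYHA), HRQL, and depressive symptoms". The next step is "Once complete, the RA will randomize the patient". The Allocation section gives the same order. Decisional Conflict and knowledge are not in this set.

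**Visit one** (Baseline measurements): "Patients randomized to the intervention group will complete the PtDA and decision quality measures (values, decisional conflict, and knowledge"). The usual care group completes Decisional Conflict and knowledge at the same visit without the aid. On timing, "Both groups will complete these measures prior to specialist consultation if feasible".

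**Visit two**: both measures are repeated in both arms within two weeks after the consultation. No other administration is described.

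**Analysis** (Data collection, management and analysis): Decisional Conflict is the decision quality outcome named. An independent-sample t-test at two time points is mentioned. The first comparison is then described as within group, and the second as "between group differences in the change scores using analysis of covariance (ANCOVA) that adjust for baseline scores".

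**Use of the result** (Evidence to inform the calculation of a sample size for a larger trial): "we will identify clinically significant differences in the change scores of decision quality measures (Decisional Conflict").

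**The concern.** An ANCOVA covariate should be unaffected by treatment. Here the score that has to serve as baseline is collected once allocation is known and, as the sentence is naturally read, once intervention patients have worked through the aid. The aid is meant to act before the consultation, so part of its effect would already be in this score. Subtracting the score and adjusting for it moves the contrast away from the aid against usual care. It moves towards what the consultation adds once the aid has been used.

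The allowance for feasibility adds a second problem: some forms labelled pre-consultation could be completed after the consultation.

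At stake is the effect-size information that the pilot is meant to pass to the larger trial.

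**Working it through.** **No planned figure to reproduce.** The 80 patients (2 × 40) rest on feasibility; no effect size, SD or power is given. Every effect and correlation below is an assumption.

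**Formula.** Let X be the visit-one score and Y the post-consultation score, with equal SDs and within-arm correlation r. Effects are reductions in Decisional Conflict in SD units: d_pre on X and d_post on Y. Regressing Y − X on arm and X gives the same arm coefficient as regressing Y on arm and X. The within-arm slope of Y on X is r, so:

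- ANCOVA arm coefficient = d_post − r × d_pre
- raw change contrast = d_post − d_pre
- with a covariate taken before randomisation, d_pre is replaced by 0 and the coefficient is d_post.

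**Assumed d_pre = 0.40 SD, r = 0.5 to 0.7.**

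| Course after the consultation | d_post | ANCOVA, r = 0.5 | ANCOVA, r = 0.7 | Raw change contrast |
|---|---|---|---|---|
| Effect fully persists | 0.40 | 0.40 − 0.20 = 0.20 | 0.40 − 0.28 = 0.12 | 0 |
| Usual care catches up by half | 0.20 | 0.20 − 0.20 = 0.00 | 0.20 − 0.28 = −0.08 | −0.20 |

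In the first row, 0.20/0.40 = 50% and 0.12/0.40 = 30% of the effect remains. In the second row, a real benefit of 0.20 SD is estimated as nothing or as slight harm.

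**Simulation check.** 40 per arm, 6,000 trials per cell, two-sided 5%, assumed d_pre = 0.50 SD:

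| r | d_post | Planned model: mean estimate (theory) | Planned model: rejection rate | Pre-randomisation covariate: mean estimate | Pre-randomisation covariate: rejection rate |
|---|---|---|---|---|---|
| 0.3 | 0.50 | 0.354 (0.350) | 0.357 | 0.501 | 0.637 |
| 0.5 | 0.50 | 0.252 (0.250) | 0.233 | 0.503 | 0.725 |
| 0.7 | 0.50 | 0.148 (0.150) | 0.144 | 0.504 | 0.874 |
| 0.3 | 0.00 | −0.152 (−0.150) | 0.105 | 0.003 | 0.052 |
| 0.5 | 0.00 | −0.247 (−0.250) | 0.228 | −0.001 | 0.056 |
| 0.7 | 0.00 | −0.350 (−0.350) | 0.546 | −0.001 | 0.049 |

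The simulation agrees with the formula. In the last three rows usual care has caught up completely, so the arms do not differ after the consultation. The planned model nevertheless reports apparent harm.

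**Illustration for the larger trial.** Assume r = 0.6, a persistent 0.40 SD effect and 90% power at two-sided 5%. The residual SD is √(1 − 0.36) = 0.8. The planned model returns 0.40 × (1 − 0.6) = 0.16 SD, standardised 0.16/0.8 = 0.20, or about 527 per arm. A genuine baseline returns 0.40 SD, standardised 0.40/0.8 = 0.50, or about 86 per arm. This also assumes that a pre-randomisation score would correlate with the post score at the same r.

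**The case against.** **Order within visit one.** The article never says outright that the scale follows the aid. That is inferred from the order of the sentence and from values being rated only in the intervention arm. If the scale were completed just before the aid, d_pre would be close to zero and most of the bias would go. This stands as a limit on certainty. It does not remove the point: measurement after randomisation is explicit, and nothing places the score before the aid.

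**The t-test.** An independent-sample test at two time points could be a between-arm comparison before and after the consultation, which would need no such covariate. A reader might therefore go too far in calling the ANCOVA the only between-arm analysis. But the following sentence calls the first comparison within group, so the text does not clearly supply a valid between-arm contrast.

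**Knowledge.** The timing of first measurement is the same for knowledge. A reader might infer that its analysis is distorted too, but no ANCOVA of knowledge is stated.

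**Blinding.** One might infer that "Participants and the RA will not be aware of treatment assignment during baseline data collection" is contradicted. It can be wholly true of the set collected before randomisation, so no contradiction is established.

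**Pilot status.** The primary purpose is feasibility, and none of the four success criteria uses this model. That stands and lowers the severity. The section on sizing the larger trial also speaks of clinically significant differences, so the larger trial need not be sized on the ANCOVA point estimate.

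**Conclusion.** The point holds for Decisional Conflict. The only score available as baseline is post-randomisation and probably post-aid, and the planned change-score ANCOVA both subtracts it and adjusts for it. If the aid works before the consultation and its effect persists, the estimate falls to 50% to 30% of the true value for an assumed r of 0.5 to 0.7. With catch-up in usual care it can reach zero or change sign.

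It would be too strong to say that the model always adjusts the aid's effect away. A fully persistent effect is attenuated, not removed; zero or reversal needs the further assumption of catch-up. The contrast of 527 with 86 per arm is likewise an illustration, not a forecast, because its effect, correlation and power are all assumed.

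Severity is should-fix: the error affects the secondary effect-estimation aim, not the feasibility decision.

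**What to change.** 1. **Analysis wording.** State that arms are compared on Decisional Conflict separately at the pre-consultation and post-consultation time points, adjusting only for variables collected before randomisation (for example the SF-36v2 mental score and CES-D). Do not subtract or adjust for the post-randomisation score. This needs no new data and covers patients already enrolled.
2. **Patients still to be enrolled.** Give the Decisional Conflict Scale after consent and before randomisation, and use that score as the covariate. The cost is one extra short questionnaire at an existing visit and a protocol modification. As the trial is already enrolling, this baseline would exist only for later enrollees.
3. **Late forms.** Do not analyse a pre-consultation form completed after the consultation as a pre-consultation score. This is analysis wording only.
4. **Larger trial.** Base the effect-size and variance information on the comparisons in items 1 and 2 instead of the current change scores.

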### Visit two - post consultation

After confirming completion of the specialist consultation, the RA will contact participants for visit two. We will measure decisional conflict and knowledge in both groups (within two weeks post-consultation). Preparation for decision-making will be measured in the intervention group. Where feasible, and participants are in agreement, the RA will arrange to conduct a brief semi-structured interview to gain additional qualitative feedback about the PtDA and process*.*

### Feasibility outcomes and measures

The primary feasibility outcomes will focus on *processes* (referral rates, recruitment rates, successful and timely delivery of the decision aid, randomization procedures, the monitoring of *resources* (budget), and study *management* (trial coordination, human resources) [62] (see above).

### Decision quality measures (knowledge, values, preferences, decisional conflict)

To measure patients’ values, we will ask patients (intervention group) to rate the personal importance of benefits, harms, and preferences using a rating scale (0 to 10). Values item selections will be developed by the core panel based on ICD evidence [30,67], the Delphi, and clinical expertise. We will also measure all patients pre-consultation preferences (get a device, don’t get a device). Knowledge will be measured both pre and post consultation in both groups using five questions related to treatment, benefits, and risks. Initial reliability and validity testing of the knowledge test will take place during the feasibility testing. Finally, to measure decisional conflict, we will use the Decisional Conflict Scale [68,69]. The scale measures a person’s perception of the difficulty in making a decision, the extent to which they feel uncertain about treatment options, are knowledgeable about the risks and benefits of options, clear about personal values, and supported in decision making [68]; the scale has demonstrated good reliability (Cronbach’s alpha coefficients > 0.78) and predictive validity [69]. Higher scores indicate greater decisional conflict and patients experiencing decisional conflict are more likely to change their minds, delay decisions, express regret, and fail knowledge tests [69,70].

### Decision preparation scale

Preparedness (intervention group), will be measured using the Preparation for Decision Making scale [59,71,72] which has ten items assessing patient’s perceptions of how useful a decision aid is in preparing them to communicate with their practitioner during consultation. The scale has demonstrated good internal consistency reliability (Cronbach’s alpha 0.92 to 0.96).

### Evidence to inform the calculation of a sample size for a larger trial

The pilot RCT will inform estimates of effect sizes and variance for a larger trial. More specifically, we will identify clinically significant differences in the change scores of decision quality measures (Decisional Conflict) that correspond to acceptable levels of patient uncertainty about their course of action (treatment options).

### Final follow-up

Three months after participants complete their baseline visit 1, the RA will confirm vital status, and device implant status from the health record.

### Data collection, management and analysis

Results for feasibility outcomes including participant recruitment, referral rates, patient uptake of the decision aid, and missing data will determine feasibility of study processes. This will mainly be descriptive in nature. Continuous variables will be summarized using descriptive statistics and measures of central tendency (means, standard deviations) and categorical variables using percentages and frequencies. Assumptions of the normality of data will be assessed. When normality assumptions are not met, non-parametric tests will be applied [73]. To determine differences in decision quality (Decisional Conflict) each group’s scores will be compared using independent sample *t*-test at two time points. The first comparison will be within group (pre and post consultation) followed by 2) between group differences in the change scores using analysis of covariance (ANCOVA) that adjust for baseline scores [73]. All quantitative tests will be two-sided and conducted at the 5% level of significance. We will also use knowledge scores > 66% to predict decision choice using logistic regression techniques. To examine associations between baseline HRQL, depressive symptoms, and 1) decision choice, and 2) values, we will use regression analysis and calculation of odds ratios and 95% confidence intervals where appropriate. SAS 9.2 (Cary, NC, USA) will be used to conduct quantitative analyses.

Qualitative data (interviews, field notes) will be analyzed using interpretive descriptive analysis [74-76]. Interviews will be recorded, transcribed verbatim, and anonymized. NVivo (http://www.qsrinternational.com/contact.aspx) software will assist with the management and coding of findings. We will analyze patient interviews to identify themes surrounding patient perceived barriers to decision aid uptake.

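### Decisional Conflict is first tested within each arm across the specialist consultation; this test cannot show an effect of the decision aid and should be descriptive only (minor)

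*Protocol article*

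**What the plan says.** The section on data collection, management and analysis sets out the Decisional Conflict analysis. Each group's "scores will be compared using independent sample" t-tests at two time points, and then: "The first comparison will be within group (pre and post consultation) followed by 2) between group differences in the change scores". The between-group step is "between group differences in the change scores using analysis of covariance (ANCOVA) that adjust for baseline scores". The stated aim of the sequence is to find differences in decision quality, and "All quantitative tests will be two-sided and conducted at the 5% level of significance".

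The timing comes from three other sections:

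- *Baseline visit*: the study is introduced "prior to their consultation in which the decision may be discussed/made". The data listed there as collected before randomisation are demographics, medical history, NYHA class, HRQL and depressive symptoms. Decisional Conflict is not among them.
- *Visit one*: "Patients randomized to the intervention group will complete the PtDA and decision quality measures (values, decisional conflict, and knowledge"). Usual care completes decisional conflict and knowledge. "Both groups will complete these measures prior to specialist consultation if feasible".
- *Visit two*: "We will measure decisional conflict and knowledge in both groups (within two weeks post-consultation").

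**The concern.** The within-arm test uses one arm's own two scores. The randomised contrast, PtDA before the consultation versus usual care, does not enter it. What separates the two scores in both arms is the consultation, at which the decision may be made. The scale covers uncertainty about options, feeling informed and feeling supported, and a consultation can plausibly move all of these without any aid.

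In the intervention arm there is a second difficulty. The first score is taken at the visit where the aid is used, and apparently after it. If so, the within-arm change leaves out whatever the aid did before the consultation. An aid that works early leaves its own arm less room to fall, so the pair of within-arm tests can favour usual care.

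At stake is how the pilot's Decisional Conflict results are read and carried into the larger trial, since the sample-size section intends to use change scores on this scale. The feasibility verdict itself is not at stake.

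**Working it through.** **Plan's own figure.** The only number to reproduce is the sample size: 2 × 40 = 80, which agrees with 1:1 allocation. It was set on feasibility grounds, with no effect size, SD or power to re-derive.

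**Inputs.** From the article: 40 per arm, two-sided 5%, consultation between the scores in both arms. Assumed, because the article gives no values: SD 1 for both scores; pre/post correlation r = 0.3, 0.5, 0.7; a fall d due to the consultation, equal in both arms; no effect of the aid.

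**Paired test.** The standardised change is d / √(2(1 − r)) and the noncentrality is that times √40. For d = 0.5, r = 0.5: 0.5 / 1 = 0.5, and 0.5 × 6.32 = 3.16 against a critical t (39 df) of 2.02, giving 87%.

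**Independent-sample test on the same patients.** The test uses the standard error √(2/40) = 0.224, whereas the true standard error of the mean change is √(2(1 − r)/40), which is 0.158 at r = 0.5. For d = 0.5: (0.5 − 1.99 × 0.224) / 0.158 ≈ 0.35, so about 64% by normal approximation; simulation (10,000 trials) gives 63%.

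Chance that the test in the PtDA arm is significant although the aid does nothing, over r = 0.3 to 0.7:

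| Consultation shift | Independent-sample | Paired |
|---|---|---|
| 0 | 0.1–2% | 5% |
| 0.2 SD | 3–10% | 18–36% |
| 0.3 SD | 14–23% | 35–67% |
| 0.4 SD | 37–41% | 55–89% |
| 0.5 SD | 61–67% | 74–98% |
| 0.8 SD | 97% or more | 98% or more |

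**Where it passes 50%.** Independent: d ≈ 1.99 × 0.224 = 0.45 SD. Paired: d ≈ 2.02 × √(2(1 − r)/40), which is 0.38, 0.32 and 0.25 SD for r = 0.3, 0.5 and 0.7.

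**At 80% completion** (32 per arm), d = 0.5, the paired figure at r = 0.5 falls from 87% to 78% and the independent figure is about 50%.

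**Exactly one arm significant, arms identical.** This is 2p(1 − p). At d = 0.5 the independent test gives 2 × 0.631 × 0.369 = 47% at r = 0.5. The paired test gives 38%, 23% and 4% for r = 0.3, 0.5 and 0.7.

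**Between-arm ANCOVA, inert aid.** Simulated rejection is 4.6% to 5.4% at every shift, so the randomised comparison is sound in that case.

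**Between-arm ANCOVA when the first score follows the aid.** Suppose the aid lowers the pre-consultation score by 0.4 SD and both arms end at the same mean. The adjusted difference is 0 − r × (−0.4) = +0.4r: +0.20 SD against the aid at r = 0.5 and +0.28 SD at r = 0.7, significant in about 17% and 39% of pilots. An analysis of change without adjustment would show the full +0.4 SD against the aid. In the same scenario (r = 0.5), the within-arm tests are significant for usual care alone in about 63% (independent) or 79% (paired), and for the PtDA arm alone in about 1%.

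**The case against.** The strongest reply is that no harm is written into the plan. Four parts of it stand:

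- A reader might infer that a significant fall in the PtDA arm will be presented as an effect of the aid, or that arms will be compared by which one reaches significance. The article says neither. The between-group ANCOVA is planned in the same sentence, and listing one comparison first sets up no hierarchy.
- The pilot's purpose is feasibility. All four success criteria are process rates, and none uses a Decisional Conflict p-value.
- A reader might infer that the within-arm test will come out significant whatever happens. That needs an assumed shift; at 0.3 SD the independent-sample test is significant in only 14–23% of pilots. The conceptual framework section gives improved decision quality as an aim of counselling, not as a measured effect.
- Regression to the mean might be offered as a further cause of a fall. Eligibility does not select on Decisional Conflict, so there is no reason to expect it in an arm's mean.

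The t-test sentence is also unclear: it could mean comparing the groups at each of two time points. That is why both tests are shown. Choosing the paired test does not help, because it rejects more often.

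What the reply does not remove is structural. At no size of shift does the within-arm test estimate the randomised effect, yet the plan gives it a 5% test under the aim of finding differences in decision quality and states no limit on its reading. Nor is it enough to point to the ANCOVA as planned, if its baseline is a score taken after the aid.

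**Conclusion.** The point holds and is minor. The within-arm pre/post test measures change across the consultation and cannot isolate the PtDA. How often it would be significant with an inert aid depends on an undocumented shift: usually not at 0.2 SD or below, more often than not from about 0.25 to 0.38 SD (paired, depending on r) or 0.45 SD (independent-sample), and almost always at 0.8 SD. These figures assume normal scores, equal SDs, a shift common to both arms and r between 0.3 and 0.7.

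That the intervention arm's first score follows the aid is the natural reading of the Visit one section, which names the aid before the measures, but the order is not stated outright. The bias in the baseline-adjusted comparison depends on that reading and on the aid having an early effect. With an inert aid the ANCOVA keeps its 5% level.

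**What to change.** In the section on data collection, management and analysis:

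1. Delete the within-arm significance tests. Report each arm's pre-consultation, post-consultation and change means in Decisional Conflict with 95% CIs, labelled as description.
2. State that anything said about the effect of the PtDA rests on the randomised between-arm difference with its 95% CI.
3. Analyse the pre-consultation and post-consultation scores each as an outcome. Do not adjust for, or take change from, a Decisional Conflict score measured after the aid. Keep the baseline-adjusted ANCOVA only if the score is confirmed to precede the aid.
4. In the Visit one section, state whether the intervention arm completes the scale before or after using the PtDA.

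The cost is wording. The same data are collected and reported, two p-values are dropped, and visits and sample size do not change.

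### Decisional Conflict is assigned an independent-samples t-test, but the first comparison is described as pre/post within each group, where the same patients give both scores

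*Protocol article*

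**What the plan says.** The Protocol article (Data collection, management and analysis) states that for Decisional Conflict "each group’s scores will be compared using independent sample *t*-test at two time points". The following sentence sets out two comparisons: "The first comparison will be within group (pre and post consultation) followed by 2) between group differences in the change scores", the second of these by "analysis of covariance (ANCOVA) that adjust for baseline scores". All tests are two-sided at 5%, and unspecified non-parametric tests replace them where normality is not met.

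Three other sections show who supplies the scores:

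- Baseline measurements, on the decision quality measures, which include decisional conflict: "Both groups will complete these measures prior to specialist consultation if feasible".
- Visit two - post consultation: "We will measure decisional conflict and knowledge in both groups (within two weeks post-consultation".
- Blinding, among the outcomes measured in both groups: "decisional conflict pre/post, and decisional outcomes".

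The planned size is given under Participants, setting, and sample size: "we will enroll 80 patients (40 per arm) over 10 months". It rests mainly on feasibility. The article names no paired t-test, signed-rank test or repeated-measures model.

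**The concern.** An independent-samples t-test assumes that the two sets of scores come from different, unrelated people. A pre/post comparison inside one arm breaks that assumption by design, because each patient contributes one score to each side and the two scores will normally be correlated. The test ignores that correlation and treats 40 pairs as 80 separate observations (78 degrees of freedom instead of 39).

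This is not a detail left to a fuller document. The article names a specific method, and that method does not suit the comparison it then describes. An analyst who follows the text literally would report intervals and p-values for the within-arm change that do not reflect its precision. With positive correlation, a change that the data do show could be reported as not significant.

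**Working it through.** **1. Which test belongs to which comparison.** Two methods are named (independent-samples t-test, ANCOVA) and two comparisons are listed (within group, between groups). The ANCOVA is tied explicitly to the between-group comparison. That leaves the t-test for the within-group one.

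**2. Are the scores paired?** Yes. The Baseline measurements and Visit two sections have both groups complete the scale before and after the consultation, and the Blinding section lists it as a pre/post measure.

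**3. Inputs.** From the article: n = 40 per arm, two-sided 5%. Assumed, because the article gives none of them: the pre/post correlation r, equal SDs at the two times, bivariate normal scores, 40 complete pairs per arm, and the size of any true change. The plan gives no figure for this test that could be reproduced.

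**4. Standard error of the mean change, in SD units.**

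- Independent test: sqrt(2/n) = sqrt(2/40) = 0.224, whatever r is.
- Paired test: sqrt(2(1 − r)/n).
- Ratio: 1/sqrt(1 − r).

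| assumed r | SE independent | SE paired | ratio |
|---|---|---|---|
| 0 | 0.224 | 0.224 | 1.00 |
| 0.3 | 0.224 | 0.187 | 1.20 |
| 0.5 | 0.224 | 0.158 | 1.41 |
| 0.7 | 0.224 | 0.122 | 1.83 |

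The ratio does not depend on n, so incomplete pairs would widen both standard errors without changing it.

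**5. Actual type I error at nominal 5%** (simulation, 40 pairs, at least 50,000 samples per setting).

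| assumed r | independent test | paired test |
|---|---|---|
| 0 | 5.0% | 4.9% |
| 0.3 | 2.0% | 4.8% |
| 0.5 | about 0.65% | 5.0% |
| 0.7 | 0.07% (about 0.1%) | 4.9% |

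**6. Power.** For a true change of 0.4 SD at r = 0.6, the paired SE is sqrt(2 × 0.4/40) = 0.141, so the change is 0.4/0.141 = 2.83 standard errors. Paired power is then about 79% (39 degrees of freedom). The independent test uses 0.224, and its simulated power is 38% to 39%. For a 0.3 SD change the figures, independent against paired, are 22% against 34% (r = 0.3), 19% against 46% (r = 0.5) and 13% against 67% (r = 0.7).

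**7. Direction.** For positive r, the usual case for a scale repeated on the same person, p-values are too large and intervals too wide. False positives do not rise. The point estimate of the mean change is the same under either test when the pairs are complete.

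**The case against.** **The t-test may be meant for something else.** The first sentence is loosely written. It can be read as comparing the two arms at each of the two time points, where an independent-samples t-test would be valid. This is a fair reading of that sentence alone. However, the next sentence calls the first comparison within group, and under this reading that comparison is left with no method. The text needs correcting either way, so this objection limits how firmly one can say the p-value will be wrong but does not remove the point.

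**Little depends on this test.** This stands. The primary outcomes are feasibility processes and are analysed mainly descriptively. None of the four success criteria uses this p-value, and 80 patients were not chosen to power it. Both arms also have the specialist consultation between the two measurements, so a within-arm change cannot isolate the effect of the aid in any case.

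**Two stronger readings that a reader might infer.** One is that the larger trial would be planned without an SD of change. The t-test itself does not yield one, but the plan summarises continuous variables with means and SDs and analyses change scores. Nothing says that planning variances will come from the within-group test.

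The other is that all conclusions about the aid should therefore move to the ANCOVA. The article does not support that without further thought. Decisional conflict is not among the items listed as collected before randomisation under Baseline visit. The Baseline measurements section has patients already randomised to the intervention complete the aid together with this scale. The score used as baseline may therefore follow use of the aid, and adjusting for it could remove part of the effect.

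**Conclusion.** The point holds as a mismatch between the named test and the comparison described. Read as written, the within-arm comparison uses a standard error too large by 1/sqrt(1 − r), or 20% to 83% for r between 0.3 and 0.7, and a test that runs at about 2% to 0.1% in place of 5%. Read the other way, the comparison has no test and the two sentences contradict each other.

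The size rests on an assumed correlation, equal SDs and 40 complete pairs per arm. Pre-consultation completion is only planned where feasible, so there may be fewer pairs. At r = 0 the two tests nearly coincide.

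Severity is minor to moderate. A reader might infer that the trial's main results are invalid or that false positives are inflated. Neither follows: with positive correlation the error is conservative, and the mean change, the between-arm ANCOVA, the feasibility outcomes and the sample size do not depend on this test.

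**What to change.** Replace the sentence that assigns the t-test with wording to this effect: within each arm, the change in Decisional Conflict from before to after the consultation will be analysed with a paired t-test (Wilcoxon signed-rank test if normality of the changes is not met), reported as mean change with 95% CI and labelled descriptive. State that independent-samples methods are used only for comparisons between arms. If arm comparisons at each time point were also intended, list them as separate comparisons with their own method.

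The cost is one or two sentences of analysis text, with no extra data, visits or patients.
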